### Sample size

We powered the study to assess whether the intervention would reduce the incidence of ARDS. Based on available evidence, we estimate a 30% risk of ARDS in the control group [2]. We are looking for an ARDS 10% absolute reduction in the intervention group. Assuming 80% power and two-sided alpha = 0.05, 226 participants would be needed to detect the resulting reduction of ARDS from 30% in the control group to 20% in the intervention group. We adopted a sample size of 252 (126 per group) to compensate for the potential loss to follow-up of some participants.

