## Background

Patients with coronavirus disease 2019 (COVID-19) infection are at risk of developing pneumonia, acute respiratory distress syndrome (ARDS), multi-organ failure, septic shock, and death. ARDS is a consequence of an alveolar injury producing diffuse alveolar damage. Cytokine storm is involved in the development of ARDS in COVID-19 patients [1]. This cytokine storm in COVID-19 is characterized by an excessive inflammatory response to SARS-CoV-2 caused by a dysregulated immune system of the host. Around 30% of COVID-19 patients with mild symptoms at presentation will progress to severe life-threatening disease largely due to ARDS [2]. Early control of the cytokine storm through therapies is essential to prevent mortality in patients with COVID-19 [3–5].

Corticosteroids such as dexamethasone inhibit the host’s excessive inflammatory response via its anti-inflammatory properties. Based on the Guidelines of the Society of Critical Care Medicine/European Society of Intensive Care Medicine (SCCM/ESICM), the use of systemic glucocorticoid therapy in ARDS is recommended for patients who are relatively early in the disease course (within 14 days of onset) and who have persistent or refractory moderate to severe ARDS (partial arterial pressure of oxygen/fraction of inspired oxygen [PaO2/FiO2] ratio < 200), despite initial management with standard therapies, including low tidal volume ventilation [6]. Corticosteroid treatment in ARDS was associated with a significant reduction in biomarkers of systemic inflammation, reduction in the duration of mechanical ventilation, and reduction in-hospital mortality [7–10]. In addition, the disease resolution is faster with early initiation of glucocorticoid (< 7 days) compared with late initiation.

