### Primary outcome

The primary outcome is a composite of development of moderate or more severe ARDS and all-cause mortality during the 30-day period following enrolment. Based on the Berlin criteria, moderate ARDS is defined by a PaO2/FiO2 > 100 mmHg and ≤ 200 mmHg, and severe ARDS a PaO2/FiO2 < 100 mmHg [26]. To determine the ARDS development, PaO2/FiO2 ratio will be monitored at least once daily. Site investigators will be reporting patient status at 30 days, irrespective of whether the patient continues hospitalized, or is discharged home. If patients are discharged alive from the hospital before day 30, the local investigator will contact the patient or relatives by phone to ensure the status of the patient on day 30 after randomization. Readmission with moderate ARDS and mortality during 30-day after randomization will be detected on the follow-up telephone call programme. Before placing a call, the patient medical record will be reviewed. Electronic health record data related to any inpatient or emergency department revisits within 30 days after discharge will be extracted.

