## Discussion

Up to one-third of patients with mild COVID-19 pneumonia develop ARDS [13]. In 25% of these patients, ARDS progresses rapidly, requiring urgent care in intermediate respiratory care or intensive care units [29]. Based on initial findings from the first reports from Wuhan, the use of systemic corticosteroids was not recommended in the treatment of patients with COVID-19 pneumonia, even in those at risk of ARDS [30]. However, the RECOVERY trial marked an inflexion point in the use of corticosteroids for the treatment of COVID-19 patients. The benefit was clear in patients with oxygen needs and in those treated more than 7 days after symptom onset, when inflammatory lung damage is likely to have been more common. No benefit in patients who did not require respiratory support was observed, according to the trial’s findings. Due to the elevated risk of progression to ARDS by approximately 30% of patients with COVID-19 pneumonia [2], identification of factors that allow for early identification and treatment of patients who will progress to ARDS is crucial. Inflammatory biomarkers such as LDH, CRP, and lymphocyte are independently associated with increased risk of severe disease [31], so tracking these markers might allow early identification or even prediction of ARDS Unfortunately, the RECOVERY trial did not collect laboratory biomarkers. Although early administration of corticosteroids could blunt the immune response in the initial stage of viral replication, the benefit of dexamethasone in this specific subpopulation of COVID-19 patients with hyperinflammation could be underestimated.

To test this hypothesis, we are conducting a trial to evaluate if the administration of dexamethasone in hospitalized patients with COVID-19 pneumonia who do not require supplementary oxygen and are at risk for severe disease leads to a decrease in the progression to ARDS and death. To our knowledge, this is the first prospective randomized controlled trial to evaluate the benefit of corticosteroids in this subgroup of patients with COVID-19.

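### The sample size is planned on ungraded ARDS (30% to 20%), but the primary endpoint is moderate-or-worse ARDS or death by day 30, and no control rate is given for that composite

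*Protocol article*

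**What the plan says.** The Sample size section names the event it plans for: "We powered the study to assess whether the intervention would reduce the incidence of ARDS". The control rate follows: "Based on available evidence, we estimate a 30% risk of ARDS in the control group [2". So does the target: "We are looking for an ARDS 10% absolute reduction in the intervention group". From these, with 80% power and two-sided alpha 0.05, it derives 226 participants, raised to 252 (126 per group) for loss to follow-up. It mentions no severity grade, no deaths and no time window.

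The Primary outcome section defines a different event: "The primary outcome is a composite of development of moderate or more severe ARDS and all-cause mortality during the 30-day period following enrolment". It sets the threshold by the Berlin criteria: "moderate ARDS is defined by a PaO2/FiO2 > 100 mmHg and ≤ 200 mmHg", with severe ARDS below that range. The Abstract gives the same composite, and the Statistical analysis section tests the primary endpoint with a chi-squared test.

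The source of the 30%, reference 2, is cited twice more. The Background says: "Around 30% of COVID-19 patients with mild symptoms at presentation will progress to severe life-threatening disease largely due to ARDS [2". The Discussion says: "Due to the elevated risk of progression to ARDS by approximately 30% of patients with COVID-19 pneumonia [2".

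**The concern.** A control rate and a target difference have meaning only for the event they describe. Here the planned event and the tested event differ in two ways. The composite excludes ARDS with PaO2/FiO2 above 200 mmHg, and it adds death from any cause.

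The 30% also has no fixed meaning within the article. The one source is used for severe life-threatening disease in patients with mild symptoms, for ARDS in patients with COVID-19 pneumonia, and for ARDS in this trial's control group. The trial's own population is narrower than either of the first two: inpatients with pneumonia, not needing oxygen, with at least two of three risk biomarkers (Inclusion criteria, Table 1).

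The power claim for the primary analysis is at stake. If the composite's control rate is not 30%, then the planned number of events, the relative effect implied by 10 points, and the power all change. A reader of a null result could not tell what effect the trial had been able to detect.

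**Working it through.** **1. The two events side by side**

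| | Sample size section | Primary outcome section |
|---|---|---|
| ARDS | no grade stated | moderate or severe only (PaO2/FiO2 ≤ 200 mmHg) |
| Death | not included | any cause |
| Window | not stated | 30 days |
| Control rate | 30% | none stated |
| Target | 10 points absolute | none stated |

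No section of the article connects the right-hand column to the 30% or to the 10 points.

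**2. Direction of the difference**

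- Excluding mild ARDS lowers the rate, if the 30% includes mild ARDS.
- Adding deaths without moderate-or-worse ARDS raises it.
- Requiring two risk biomarkers may raise it. The Background says that progression occurs particularly in patients with such biomarkers.
- Under the Intervention section, controls who come to need oxygen receive corticosteroids. This may lower the rate relative to the source, but steroid use in the source is not given.

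The net direction is undetermined.

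**3. The plan's own figure**

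Inputs from the Sample size section: p1 = 0.30, p2 = 0.20, two-sided alpha 0.05 (z = 1.960), power 80% (z = 0.842), allocation 1:1. With p̄ = (p1 + p2)/2 = 0.25:

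n per arm = [1.960·√(2·p̄(1−p̄)) + 0.842·√(p1(1−p1) + p2(1−p2))]² / (p1−p2)²

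= [1.960·√0.375 + 0.842·√0.37]² / 0.01 = 293.2, rounded up to 294 per arm, or 588 in total.

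The stated 226 is not reproduced. Other two-sided versions give totals of 582 (unpooled), 584 (arcsine) and 626 (continuity-corrected). This is a separate error, but it sets the starting point for the power figures below.

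**4. Power at 126 per arm**

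Power = Φ{ [|p1−p2| − 1.960·√(2p̄(1−p̄)/n)] / √[(p1(1−p1) + p2(1−p2))/n] }

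At 0.30 versus 0.20 with n = 126: (0.1000 − 0.1069) / 0.0542 = −0.128, so power is 45%.

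**5. Range of assumed control rates for the composite**

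The document gives no rate for the composite, so every rate here is an assumption. The effect is held in two ways: as the risk ratio implied by 30% to 20% (2/3), and as the stated 10 points.

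| Control rate | Expected control events (126 × rate) | Power, risk ratio 2/3 | Power, 10-point reduction | Relative reduction implied by 10 points |
|---|---|---|---|---|
| 15% | 19 | 22% | 76% | 67% |
| 20% | 25 | 29% | 60% | 50% |
| 30% | 38 | 45% | 45% | 33% |
| 40% | 50 | 61% | 38% | 25% |

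The two columns move in opposite directions. Both the control rate and the scale of the effect therefore have to be stated for the endpoint actually tested.

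**The case against.** The strongest defence is that the 30% may already describe something close to the composite. The Background uses the same source for severe life-threatening disease, which is nearer to PaO2/FiO2 ≤ 200 mmHg or death than to ARDS of any grade. That the 30% includes mild ARDS is only an inference from the missing grade, and the source is not available to check. This stands. It means that the figure cannot be called too high, but it does not supply a rate for the composite, and the Discussion and the Sample size section both call the same figure ARDS.

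A reader might go further and infer that the composite's control rate must be below 30%. The document does not support that, because deaths and biomarker selection may push the rate up.

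A reader might also multiply 30% by the 25% in the Discussion ("In 25% of these patients, ARDS progresses rapidly, requiring urgent care in intermediate respiratory care or intensive care units [29"), take the resulting 7.5% as a lower bound, and conclude that a 10-point reduction could not occur. That 25% concerns rapid progression and level of care, and comes from another source. It is not the share reaching PaO2/FiO2 ≤ 200 mmHg, and a patient who worsens slowly can still meet the endpoint. The article therefore gives no basis for the 7.5% bound or for the conclusion drawn from it.

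Finally, it is fair to object that holding a risk ratio of 2/3 departs from the stated absolute target. On the absolute scale power rises as the control rate falls, which is why both scales are shown. Likewise, the fall from the claimed 80% to 45% at 30% versus 20% comes from the arithmetic error and not from the endpoint mismatch.

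**Conclusion.** The point holds as an endpoint mismatch of undetermined direction. The sample size rests on ungraded ARDS, the primary analysis tests moderate-or-worse ARDS or death by day 30, and the article states neither a control rate nor a target difference for the latter. The stated 80% power is therefore not established for the primary endpoint.

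Over assumed control rates of 15% to 40%, power at 126 per arm runs from about 22% to 61% for a risk ratio of 2/3, and from about 76% down to 38% for a 10-point reduction. The 76% at a 15% control rate requires dexamethasone to prevent two thirds of events. No scenario shown reaches 80%. These figures rest on the two-proportion normal approximation, full follow-up of all 252 participants, and rates that the document does not supply.

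The mismatch is separate from the arithmetic error. Raising the total to 588 would still size the trial for an event other than the primary endpoint. It should be corrected, and nothing in the article shows that the true control rate is lower than planned.

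**What to change.** In the Sample size section:

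- Name the composite (PaO2/FiO2 ≤ 200 mmHg or death from any cause by day 30) as the event the trial is sized for.
- State the control rate assumed for it in patients with at least two risk biomarkers, and the target difference, with the basis for each. Say whether the effect is meant as absolute or relative.
- Say what the 30% from reference 2 measures, and describe it the same way in the Background, the Discussion and the Sample size section.
- Restate power at 126 per arm over control rates on both sides of 30%, for example 15% to 40%.
- In the same revision, correct the calculation for 30% versus 20%, which needs about 588 participants and not 226.

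Reporting ARDS of any grade as a secondary outcome is optional. The daily PaO2/FiO2 readings would support it in hospital, but the follow-up calls are described as detecting readmission with moderate ARDS, so milder cases after discharge could be missed.

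The cost is rewording and recalculation, with no change to the data collected. The downside is that the stated power becomes less favourable. Restating it discloses the shortfall but does not remove it.

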### Randomization

Eligible, consenting patients will be randomly assigned in a 1:1 ratio to receive either dexamethasone plus standard of care (intervention group) or standard of care alone (control group). Randomization will be done within the REDCap system with unpredictability of assignments. Our statistician created a randomization schedule using a permuted block design, so equal numbers are assigned to each group. This system ensures a balanced allocation of subjects to the study arms. Records of individual assignments to each group will be de-identified (user number and centre ID instead of patients’ names), sequentially numbered, and stored on a secure computer system. Local investigators in participating centres are the only authorized personnel to interact with the radomization system through a username and password. Once eligibility is confirmed in the electronic case report form, the treatment group is assigned by the system. Dexamethasone will be provided free of charge for this study by the organization funding. According to the ethical principles for medical research of the Declaration of Helsinki, the use of no placebo (no intervention) is acceptable when no proven intervention exists. The Spanish Agency of Drugs and Medical Devices and the Ethics Committees did not mandate a blinded design or the administration of a placebo.

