### Statistical analysis

Baseline demographic and clinical characteristics will be presented in both groups. Quantitative variables will be defined by mean and standard deviation. Continuous variables will be compared using Student’s *t*-test (normal distribution) or Mann–Whitney test (non-normal distribution). Qualitative variables will be defined by frequency and compared using the chi-squared test or Fisher’s exact test. The proportion of patients that meet the primary outcome will be calculated in the control group and the intervention group. The primary endpoint will be analysed using the chi-squared test comparing the unadjusted risk ratios in each arm. The estimates of risk ratios will be adjusted with multivariate analysis by logistic regression. Adjustment will be performed for age, gender, and history of diabetes, hypertension, or obesity which are the most important factors related to the mortality and disease progression in patients with COVID-19 [27]. Study site will also be included in the multivariate analysis. As a secondary analysis, survival analysis to show the effect of dexamethasone on the primary endpoint in each arm will be performed using Kaplan–Meier curves and log-rank test. A *p*-value of less than 0.05 will be considered statistically significant. Statistical analysis will be performed with the SPSS V28.0 software (SPSS, Inc. Chicago, IL, USA). CONSORT reporting guidelines will be followed to ensure that results are presented in a complete, detailed, and systematic way.

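### The stated 226 patients give about 41% power, not 80%, for 30% versus 20% at two-sided 5%; all 252 give about 45%

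*Protocol article*

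**What the plan says.** The Sample size section of the protocol article gives a complete set of inputs.

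- Error rates: "Assuming 80% power and two-sided alpha = 0.05".
- Control rate: "we estimate a 30% risk of ARDS in the control group".
- Effect: "We are looking for an ARDS 10% absolute reduction in the intervention group".
- Result: "226 participants would be needed to detect the resulting reduction of ARDS from 30% in the control group to 20% in the intervention group".
- Allowance for loss: "We adopted a sample size of 252 (126 per group) to compensate for the potential loss to follow-up of some participants".

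The Randomization section fixes the allocation: "Eligible, consenting patients will be randomly assigned in a 1:1 ratio". The Statistical analysis section fixes the test: "The primary endpoint will be analysed using the chi-squared test comparing the unadjusted risk ratios in each arm". Under Primary outcome the endpoint is defined more widely than ARDS: "The primary outcome is a composite of development of moderate or more severe ARDS and all-cause mortality", over 30 days.

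**The concern.** A fall from 30% to 20% is a modest difference between two proportions, and 113 patients per group is far fewer than such a comparison normally takes. The article prints both the inputs and the answer, so this can be settled from the text alone and does not depend on an analysis plan or a fuller protocol.

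The stated power governs how the primary result will be read. The Background and Discussion explain that an earlier large trial found no benefit in patients without oxygen needs, and they argue that benefit in a biomarker-selected subgroup may have been underestimated. A non-significant result labelled as 80% powered could be taken as good evidence against a 10-point benefit. With power below one half it would not be.

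There is a second, smaller problem. The calculation uses the risk of ARDS, while the primary outcome counts only moderate or more severe ARDS and adds death from any cause. The power for the endpoint that will be tested is therefore never stated.

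**Working it through.** **Inputs, all from the protocol article.** Control rate p1 = 0.30, intervention rate p2 = 0.20, power 80% (z = 0.8416), two-sided alpha 0.05 (z = 1.96), from Sample size; 1:1 allocation, from Randomization; chi-squared test of two proportions, from Statistical analysis. The mean rate is 0.25.

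**1. Is 226 a total or a per-group figure?** The adopted 252 is described as 126 per group, so 252 is the two-group total, and so is the 226 from which it was inflated. No loss rate is stated, but 226/0.90 = 251.1, which rounds up to 252 and implies about 10%.

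**2. Can 226 be reproduced?** The pooled-variance formula is

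n per group = [1.96·√(2·0.25·0.75) + 0.8416·√(0.30·0.70 + 0.20·0.80)]² / 0.10²

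= [1.2002 + 0.5119]² / 0.01 = 293.2, rounded up to 294, or 588 in total.

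Other standard versions at 80% power:

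| Version | Per group | Total |
|---|---|---|
| Two-sided, pooled | 294 | 588 |
| Two-sided, unpooled | 291 | 582 |
| Two-sided, arcsine | 292 | 584 |
| Two-sided, continuity-corrected | 313 | 626 |
| One-sided, pooled | 231 | 462 |
| One-sided, unpooled | 229 | 458 |

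None gives a total near 226. The nearest match is a one-sided figure per group (229 to 231). That might be the origin of the number, but this is conjecture, and it conflicts with both the stated two-sided alpha and the 126 per group. Even 226 in each group would give only 69% power two-sided.

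**3. Power that the stated numbers deliver.** Power = Φ{[0.10·√n − 1.96·√0.375] / √0.37}.

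- n = 113: (1.0630 − 1.2002)/0.6083 = −0.226, so power is 41.1%.
- n = 126: (1.1225 − 1.2002)/0.6083 = −0.128, so power is 44.9%.

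Exact enumeration of the uncorrected chi-squared test over all binomial outcomes gives 41.4% and 45.1%. With the continuity-corrected chi-squared test it gives 35.2% and 39.7%. The same enumeration at 294 per group gives 80.3%, which confirms the method.

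**4. What the design can detect.** From a 30% control rate, 80% power needs an intervention rate of about 14.6% with 113 per group (a 15.4-point reduction) or about 15.3% with 126 (14.7 points).

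**5. Precision at the design rates.** The 95% half-width for the risk difference is 1.96·√(0.37/n), which is 11.2 points at n = 113 and 10.6 points at n = 126. Both exceed the 10-point target. The risk ratio would be 0.67, with a 95% interval of about 0.42 to 1.06 at 113 per group. An observed 30% versus 20% gives z = 0.10/√(0.375/n) = 1.736 (p = 0.083) or 1.833 (p = 0.067).

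**6. The composite endpoint.** The article gives no control rate for it, so the rates below are assumptions. With the risk ratio held at 2/3, the power is:

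| Assumed control rate | 113 per group | 126 per group |
|---|---|---|
| 15% | 20% | 22% |
| 20% | 27% | 29% |
| 30% | 41% | 45% |
| 40% | 57% | 61% |
| 50% | 72% | 77% |

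**The case against.** No reading of the text rescues 226. Covariate adjustment by logistic regression is planned, but it is not part of the stated calculation and could not plausibly lift power from about 41% to 80%. The fair objections concern what surrounds the arithmetic.

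- **The composite rate could be higher than 30%, not only lower.** The 30% is quoted for patients with mild symptoms in general. This trial requires at least two adverse biomarkers, and its endpoint adds death. Excluding mild ARDS pulls the other way. Whether the cited source counted mild ARDS cannot be checked here. This stands, and it is why the table above runs in both directions. No row reaches 80%.
- **An observed 10-point reduction is not always non-significant.** This also stands. It misses p < 0.05 at 30% versus 20%, but an observed 20% versus 10% would give p = 0.035 at 113 per group and 0.026 at 126. The statement is therefore confined to the design rates.
- **How a null result is read is a matter for the analysis plan.** Agreed: the lack of such a rule is not an error in this document. A wrong power figure is.
- **Restating the power is more than an edit.** The trial had ethics and regulatory approval and was recruiting when the article was written. This is a fair point about cost, not about correctness.

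**Conclusion.** The sample size statement is wrong on its own inputs. The total needed for 30% versus 20% at two-sided 5% and 80% power is about 588 evaluable patients, 2.6 times the stated 226 (588/226). The actual power is about 41% with 226 evaluable and about 45% if all 252 are evaluable. With the roughly 10% loss that the plan allows for, 41% is the relevant figure. This rests only on the printed rates, alpha, allocation and test, and it holds under every standard formula tried and under exact calculation. The mismatch between ARDS and the composite endpoint is an additional defect. Its effect on power can go either way, because the article gives no composite rate. The sample size paragraph must be corrected.

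**What to change.** 1. Replace the sentence claiming 80% power. State that 226 evaluable patients (252 randomised) give about 41% power for 30% versus 20% at two-sided 5%, or about 45% with no loss, and 80% power only for a fall from 30% to about 15%.
2. Base the calculation on the composite primary outcome. Justify the assumed control rate and show power over a range of rates on both sides of it.
3. State the assumed loss rate as a number.
4. If 80% power for a 10-point reduction is to remain the claim, the size must rise to about 588 evaluable, or 588/0.90 = 653.3, about 654 randomised.
5. Optionally, say in advance that a non-significant result will be interpreted from the confidence interval and not as evidence of no effect.

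Steps 1 to 3 need no extra patients. They do mean amending a justification that the ethics committee and the regulator have already reviewed, and accepting a much less favourable stated power. Step 4 would add about 402 randomised patients (654 − 252).
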